#### Standard care group

Standard care typically involves attending a cardiac rehabilitation program once a week for 6 weeks that is predominantly aerobic in nature and often features a progressive walking program and gentle range of motion exercises [9, 37]. Upper limb resistance is limited to a combined weight of < 1 kg for the first 8–12 post-operative weeks, or until the sternum unites, as per current sternal precautions. During the 12 weeks, participants in the standard care group will be referred by their respective hospital, to a hospital or community-based cardiac rehabilitation program, as per the hospital’s current cardiac rehabilitation referral procedures.

### Outcome measures

#### Primary outcome

##### Cognitive function

Improvement in cognitive function, particularly executive functioning, has been associated with exercise [11, 38–41]. Executive functioning refers to the cognitive processes, including working memory, multitasking, scheduling and planning [42]. One of the assessment instruments used to assess cognition will be the Alzheimer’s Disease Assessment Scale and cognitive subscale (ADAS-cog). The ADAS-cog is a tool that measures impairment across several cognitive domains, including language, orientation, constructional praxis, ideational praxis and memory [20]. It is sensitive to changes in cognitive impairment and progression to dementia [43]. Cognitive function using the ADAS-cog will be assessed at baseline (pre-operatively), 14 weeks post-operatively and 6 months post-operatively.

#### Secondary outcomes

##### Safety and feasibility

Recruitment rate and retention rate will be analysed to determine study feasibility. Feasibility data will be analysed as follows: recruitment rates and patient recruitment-to-screening ratio, percentage of participants who complete the intervention, overall percentage of sessions attended and number of participants who drop out of the study. Data for safety will be analysed as the number of sessions and exercises stopped due to pain, any adverse event or incident that stops the participant from completing the prescribed exercise, and any major adverse cardiac and cerebral events (MACCE). MACCE endpoints include all-cause mortality, cerebral vascular event (stroke), documented myocardial infarction or repeat coronary intervention (percutaneous coronary intervention or redo cardiac surgery), with data being collected at the 6 months.

##### Demographics

Demographic information including age, employment, education, smoking history, alcohol consumption, comorbidities, waist circumference and body mass index (BMI) will be collected at baseline.

##### Cognitive test

The Mini Mental State Examination (MMSE) is a valid tool commonly used to assess cognitive function. Mild cognitive impairment is a clinical diagnosis and is a recognised precursor to the development of dementia. Formal diagnosis involves assessment of cognition, especially of memory, and using an instrumental activities of daily living scale (such as the Lawton and Brody Instrumental Activities of Daily Living (IADL) scale) [29], with exclusion if there is a physical explanation for failure of IADL. There are multiple approaches used by clinicians to assess memory, but the MMSE is a commonly used tool. The MMSE was selected, as it separates patients with cognitive disturbances from those without, indicating level of cognitive impairment [22]. For the purposes of this trial, pre-existing cognitive impairment will be defined as:
Normal—MMSE scores 27–30 and normal IADL (score 8 females and 5 males)Mild—MMSE scores 24–26 and normal IADL (score 8 females and 5 males)Moderate—MMSE scores 18–23 and normal IADL (score 8 females and 5 males)Severe—MMSE score < 18 and impaired IADL (score < 8 females and < 5 males)

The ADAS-cog may be susceptible to floor and ceiling effects; therefore, the Mini Mental State Examination and cognitive domain of the Postoperative Quality of Recovery Scale (PostopQRS) will also be used to ascertain changes in cognition from baseline, across time points, as well as the MMSE being used to determine baseline cognitive level. This will be assessed at baseline (pre-operatively), 14 weeks post-operatively and 6 months post-operatively.

##### Quality of recovery

Quality of recovery will be measured at all data collection time points using the Postoperative Quality of Recovery Scale (PostopQRS), which is a multidimensional survey tool that assesses quality of recovery following surgery and anaesthesia [24]. The PostopQRS assesses quality of recovery over five domains including physiologic, nociceptive, functional, cognitive and emotional recovery, as well as overall patient perspective. Scoring recovery involves comparing post-surgery performance to pre-surgery baseline values. The pre-surgery baseline values serve as an excellent phenotype for patients with respect to the five domains. The scale is conducted either face-to-face whilst in hospital or via telephone interview after discharge [44]. The ability to conduct the scale via telephone makes this a highly feasible tool for extended patient follow-up. Importantly, the scale only takes 5–6 min to conduct on each occasion and does not require highly specialised staff to perform it.

Specifically, the cognitive domain examines both memory and executive function (word generation task), allowing more than just memory to be tested [45]. Because the scale has both cognitive and functional dimensions (assessment of activities of daily living), it is suitable to use as an early indicator screening tool for cognitive impairment and dementia, as cognitive impairment can be identified with or without impairment of function. Further, the scale has defined cutoff scores for low baseline cognition which can identify preoperative cognitive impairment [44]. The application of the scale is appropriate for patients having hospital admission, as it will be used to track change over time from their baseline values on admission. It is already validated and used widely and is set up for multi-user web-based access (www.postopQRS.com). Scoring of the scale is automatically conducted by the system, and individual recovery outcomes are available in real time.

Pre-operatively, the PostopQRS can be used to capture the multidimensional aspects of quality of recovery from the patient perspective. This can be used to identify the association of cognitive decline other quality of recovery parameters. Because it is a simple to perform tool that is validated for telephone use, the PostopQRS can be used to track deterioration in cognitive and functional domains over time and will complement the assessment using the ADAS-cog and MMSE scales. This will be assessed at every time point.

##### Functional tests

Activities of daily living will be assessed using the Brody and Lawton Instrumental Activities of Daily Living (IADL) instrument [29]. The Lawton and Brody IADL Scale assesses the living skills deemed necessary to live independently in the community. These skills are considered more complex than the basic activities of daily living. It is useful to determine how an individual is currently functioning and monitoring improvement or deterioration over time [29]. This test has been associated with cognitive impairment and is used in conjunction with cognitive assessments to diagnose dementia and the level of cognitive impairment; however, it has not been validated specifically in cardiac patients [29, 46]. This will be assessed at baseline (pre-operatively), 14 weeks post-operatively and 6 months post-operatively.Upper limb function will be assessed using the short-form Functional Difficulties Questionnaire (FDQs) [30]. The FDQs is a 10-item questionnaire which asks the participant to rate the difficulty they experience when completing a series of 10 upper limb and trunk activities by placing a mark along a 10-cm line, with anchors indicating “no difficulty” and “maximum difficulty” [30]. For those activities that participants could not attempt whilst completing the questionnaire due to the institution sternal precautions, they are asked to think back to the last time they performed the task [30]. Individual scores, measured to the nearest centimetre (cm), are aggregated to form a total out of 100 with higher scores representing greater difficulty experienced during functional activities. The FDQs has been reported to be reliable and valid in a cohort of cardiac surgery patients [47]. This will be assessed at baseline (pre-operatively); 2, 8 and 14 weeks post-operatively; and 6 months post-operatively.Lung capacity will be assessed through breath gas analysis [25], using a Spirobank II Advanced Spirometer (Medical International Research, Sequim, USA) to determine forced vital capacity (FVC) and forced expiratory volume in 1 s (FEV1). Each test takes no longer than 30 s to complete. The participant will be asked to breathe normally for 3 breath cycles before being asked to take a deep breath in, breathe out as hard and as fast as they can before taking another deep breath in. This will be repeated three times with the best of the three attempts recorded. All volumes will be recorded in litres. This will be assessed at baseline (pre-operatively); 2, 8 and 14 weeks post-operatively; and 6 months post-operatively.Leg strength will be assessed using isometric quadriceps and hamstring strength tests on resistance machines that stabilise the joint and isolate the muscle during testing. Each test is of 15–20-s duration to ensure safety. Peak torque is measured in Newtons, using a dynamometer placed in the shaft of the equipment. The tests will be attempted three times with the highest strength measurement recorded and noted in comparison to the age and gender normative values. This will be assessed at 2, 8 and 14 weeks post-operatively and 6 months post-operatively.Handgrip strength will be assessed using a JAMAR hand-held dynamometer and measured in kilogrammes (Sammons Preston Rolyan, Brooklyn, USA). Hand-held dynamometry is a reliable, objective tool for muscle strength measurement, and a predictor of postoperative complications, mortality, functional decline and cardiovascular risk [26]. The participant will be tested in the position recommended by the American Society for Hand Therapists (participant seated with shoulder adducted, neutrally rotated, elbow flexed to 90°). The peak value of the maximal squeeze over 5 s will be recorded. Three serial tests of maximum grip strength with the right hand will be performed, and the best of the 3 values will be recorded and noted in comparison to age and gender normative values. The test is a reliable and responsive measure for patients in cardiac rehabilitation (ICC = 0.97) [26]. This will be assessed at 2, 8 and 14 weeks post-operatively and 6 months post-operatively.Dynamic balance will be assessed using the Four Square Step Test (FSST), which requires rapid dynamic weight shifting, coordination and stepping [27, 48]. Participants will be asked to step as quickly as possible into four squares marked on the floor with red sticks in a certain sequence that requires the participant to step forward, backward and sideways. The test will be attempted three times with the fastest time taken to complete the sequence recorded in seconds. The researcher will act as a spotter, standing adjacent to the participants during the performance of the test, to reduce the possible risk of falls. Mobility issues have been found to affect a third of cardiac patients in the early post-operative period, thus increasing falls risk [13]. The FSST balance performance has been found to be predictive of future falls and is able to distinguish non-fallers from single fallers from multiple fallers in community-dwelling older adults and in numerous musculoskeletal and neurological conditions; however, it has not been validated in the surgical cardiac population [27, 28]. This will be assessed at 2, 8 and 14 weeks post-operatively and 6 months post-operatively.Physiological data will be obtained through measurement of blood pressure, heart rate and oxygen saturation at rest, at the baseline (pre-operatively); 2, 8 and 14 weeks post-operatively; and 6 months post-operatively. All blood pressure measurements will be taken from the left arm using an Elitecare single hand sphygmomanometer and blood pressure cuff and a dual head Liberty lightweight aluminium stethoscope. Should a patient’s blood pressure be unable to be taken due to pre-existing medical reasons (i.e. fistula), it will be taken on the right arm and documented as such.Heart rate and oxygen saturation will be assessed using a Heart Sure A320 Pulse Oximeter (Omron, Melbourne, AUS), a portable finger pulse oximeter.

##### Sternal stability

Sternal stability will be assessed and quantified using sternal ultrasound and the Sternal Instability Scale (SIS) [31]. This will allow the researchers to measure any sternal movement occurring and monitor patient safety prior to commencing all resistance upper limb exercise modalities.
Sternal ultrasound: Ultrasound (US) measures of sternal micromotion will be acquired by imaging the sternum at rest, cough and on each of the six upper limb resistance training exercises. This will be stored as a video file to allow analysis of data. Measurements will be made at two sites (i) at 6 cm (mid-sternum) and (ii) 10 cm (lower sternum) from the sternal notch (Additional file 4). The greatest degree of horizontal, vertical and diagonal sternal separation (mm) will be determined by a researcher with a minimum of 1-year experience in sternal ultrasound and DICOM analysis. The video will be watched and the greatest separation recorded for each movement, at each site from a still frame. Previous research has shown that ultrasound measures are a valid and reliable indicator of the separation and motion at the sternal edges in patients post-median sternotomy [32]. US has demonstrated excellent test-retest reliability with intra-class correlation coefficients ranging from 0.90 to 0.93 [32]. A Fujifilm Sonosite iViz and a L38v 9-cm 10–5-MHz linear transducer will be used to measure sternal micromotion (Fujifilm Sonosite, Brookvale, AUS). Images will be analysed using Prosolv5 Synapse Cardiovascular. This will be assessed at 2, 8 and 14 weeks post-operatively for the resistance training participants on the six upper limb resistance exercises and during a cough at baseline and 6 months post-operatively for both the resistance training and standard care groups.Sternal Instability Scale (SIS): The SIS is a physical examination test that subjectively evaluates the stability of the sternum based on a 4-point scale (Table 4) [31]. A score of 0 corresponds to a clinically stable sternum with no detectable motion or separation of the sternal edges, whilst a score of 3 corresponds to a completely separated sternum with marked increased motion or separation of the sternal edges. Patients’ initial sternal stability will be determined during rest and special testing, including cough and trunk rotation (Table 4). Whilst performing the upper limb exercises, the exercise will not be performed or the weight progressed if any increase in sternal micromotion that exceeds the score determined during the initial rest and special testing. Previous research has shown that the SIS is both a valid and reliable clinical tool for measuring the stability of the sternum in patients following a median sternotomy. It has demonstrated excellent inter- and intra-rater reliability, with intra-class correlation coefficients of 0.97 and 0.98, respectively [49]. This will be assessed at 2, 8 and 14 weeks post-operatively for the resistance training participants on the six upper limb resistance exercises. It will also be assessed when an upper limb exercise resistance is progressed and will be documented if a result other than zero (0) is found to occur.

**Table 4 Tab4:** Sternal Instability Scale

Grade of motion	Modified Sternal Instability Scale
0	Clinically stable sternum (no detectable motion)—normal
1	Minimally separated sternum (slight increase in motion upon special testing*)
2	Partially separated sternum—regional (moderate increase in motion upon special testing*)
3	Completely separated sternum—entire length (marked increase in motion upon special testing*)

*Special testing may include shoulder flexion, trunk rotation, lateral flexion, coughing and opposing movements of the upper limbs, either unilaterally or bilaterally

##### Participant satisfaction

The Global Rating of Change scale will be used to subjectively assess participant satisfaction with the exercise program at the completion of the 12-week exercise program [35]. In addition, participants will be prompted to complete eight semi-structured questions about the exercise program. Questions will explore factors impacting cardiac rehabilitation participation, including perceived facilitators, barriers, benefits to recovery and enjoyment. The responses given to these questions will undergo qualitative analysis. This will be conducted at 14 weeks post-operatively.

### Data management

Information collected from participants will be stored securely in both hard copy (paper) and soft copy (electronic). The information will be stored on paper records at the University of Melbourne in a locked cabinet, and the de-identified data entered into an electronic web-based database (www.postopQRS.com, located at City, University of London) and other research documents stored on a secure file server based at the University of Melbourne.

All database storage is protected with login and password for individual researchers. All paper records used during the study are kept after the project has been completed for a minimum of 15 years, as per Good Clinical Practice. After the 15 years, information will be disposed of via shredding of all paper records, and deletion from databanks. Re-identifiable data is used during the conduct of the study in order to contact patients for follow-up visits. The code will be kept separately to the case report forms.

### Data analysis

The objective of this pilot study is to test the feasibility of recruitment, retention, intervention and data collection, and the safety of moderate-intensity resistance training, on post-operative cognitive and functional recovery. The following parameters would indicate clinically important relative differences between groups:
Group separation: ≥ 20% difference between groups;Feasibility: screening-to-recruitment ratio < 2 and recruitment of ≥ 1 participant/site/week;Safety: adverse events and serious adverse events;Protocol compliance: ≥ 80% protocol compliance and exercise intervention commenced at two post-operative weeks;ADAS-cog: difference of at least 2 on the ADAS-cog scale; andMuscular strength: ≥ 15% improvement in strength.

The analysis will be on an intention-to-treat basis. Data collected for feasibility and safety will be analysed using descriptive statistics (mean ± standard deviation) to explore possible effects of the intervention. Mean changes in outcomes over time will be summarised graphically and descriptively within each group, with odds ratio and confidence intervals. As this is a pilot study, it is not powered to detect clinically meaningful effects. Feasibility data will be analysed to determine whether it is worth conducting a large-scale trial. A statistician not involved in the study and the student researcher will assess these parameters at the end of the trial.

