### Randomisation, allocation concealment and blinding

All participants will be randomly allocated (1:1) to either the moderate-intensity resistance training group or the control group (standard care). Randomisation will be undertaken in blocks of 4–8, using double opaque envelopes. Envelopes will be prepared by an independent person not involved in the study. Patients will be randomised prior to discharge from hospital, following baseline data collection. The assessor is responsible for delivering the resistance training intervention, in addition to outcome measure assessment at all time points; therefore, she will not be blinded to group allocation. It will also not be possible to blind participants to their respective group allocation.

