### Sample size determination

As this is a pilot study, a sample size calculation to determine the power of this study will not be performed. Instead, the focus will be on the feasibility and safety of the study. We plan to recruit a minimum of 20 participants, with an 80% retention rate.

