##### Adverse events

Adverse events will be classified as adverse events (AEs) or serious adverse events (SAEs). An AE will be defined as an incident that requires the cessation of exercise for safety reasons and is likely to be directly related to the exercise program. If an adverse event is life-threatening, requires hospitalisation and results in significantly reduced capacity or disability, or death, it will be classified as a SAE. This will be inclusive of new or unrelenting chest pain, any report of shortness of breath that does not settle quickly with rest, or acute changes in level of consciousness during the session will be considered as serious adverse events. Any serious adverse event will be immediately reported to the Ethics Committee. If there is an unacceptable risk of serious adverse events in one or both of the treatment groups, the trial will be stopped and termination may be recommended by investigators.

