Cognitive impairment is a frequent complication of cardiac surgery that is not typically addressed in cardiac rehabilitation programs. There is evidence associating resistance-based exercise programs with improved cognitive outcomes in older adults (aged 65 years and older) [38, 60] and adults with mild cognitive impairment [41, 61], providing a strong rationale for incorporating resistance training into rehabilitation training after surgery. To our knowledge, this pilot study is the first trial to comprehensively assess the safety and feasibility, cognitive recovery, physical and functional recovery and participant perceived impact of early resistance training as a form of cardiac rehabilitation. The results of this pilot study will be used to determine the feasibility of a future large-scale randomised controlled trial that promotes the integration of early resistance training into existing aerobic-based cardiac rehabilitation programs in Australia.

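### The feasibility and safety results that justify N = 20 are to be summarised as mean and SD without intervals, although about 10 trained participants leave very wide ones

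*Protocol article*

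**What the plan says.** Under Sample size determination, the protocol article states that "a sample size calculation to determine the power of this study will not be performed" and continues: "Instead, the focus will be on the feasibility and safety of the study". It then gives the size: "We plan to recruit a minimum of 20 participants, with an 80% retention rate". Under Randomisation, allocation concealment and blinding, allocation is 1:1.

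Data analysis makes feasibility and safety the pilot's objective and lists parameters for judging it. Most carry a number: group separation of at least 20%, a screening-to-recruitment ratio below 2, at least one participant per site per week, an ADAS-cog difference of at least 2, and a strength gain of at least 15%. Two entries matter here:

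- Compliance: "Protocol compliance: ≥ 80% protocol compliance and exercise intervention commenced at two post-operative weeks".
- Safety: "Safety: adverse events and serious adverse events", with no value attached.

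The same section assigns feasibility and safety data to descriptive statistics, specified as mean and SD. It mentions confidence intervals only for mean changes in outcomes over time. The feasibility data are to show whether a large trial is worthwhile.

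Safety and feasibility, under Secondary outcomes, lists both the percentage of participants completing the intervention and the overall percentage of sessions attended. It ties neither to the 80%. Under Adverse events, the stopping statement is also unquantified: "If there is an unacceptable risk of serious adverse events in one or both of the treatment groups, the trial will be stopped".

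**The concern.** A pilot may properly forgo a power calculation. This one puts feasibility and safety in its place, so those results should be reported in a way that shows what the chosen size can establish. The stated summary does not do this. Completion, retention and having an event are yes/no outcomes per participant. For such data the SD is fixed by the proportion and adds no information, and with no events it is zero, which looks like certainty.

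The results feed a decision. A reader given a bare 80% against a cut of 80%, or a bare count of zero events, has no means of seeing how weak the evidence is in about 10 trained people. A compliance figure compatible with a poor program, or an event rate that is merely unobserved, could then be carried into the case for a large trial.

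**Working it through.** **Inputs.** Total N is at least 20 (Sample size determination). Allocation is 1:1, so about 20/2 = 10 are trained. The compliance cut is 80% (Data analysis). There are 24 sessions per trained participant (Procedure and data collection). The article gives no formula behind 20; the only arithmetic to reproduce is 20 × 0.80 = 16 retained.

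**What mean and SD show.** Code compliance as 0/1. For 8 of 10 the mean is 0.80 and the SD is √[(10/9) × 0.8 × 0.2] = 0.42. For 0 events in 10 the mean is 0 and the SD is 0. Neither conveys precision.

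**Exact (Clopper–Pearson) 95% intervals.** The lower limit solves P(X ≥ x | p) = 0.025 and the upper limit solves P(X ≤ x | p) = 0.025.

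- Compliance 8/10: 44% to 97%.
- Retention 16/20: 56% to 94%.

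**Chance of meeting the 80% cut, scored per participant.** With n = 10 the cut is met at 8 or more, so the chance is P(X ≥ 8 | 10, p):

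| True compliance | 60% | 70% | 80% | 90% |
|---|---|---|---|---|
| n = 10, at least 8 | 17% | 38% | 68% | 93% |
| n = 8, at least 7 | 11% | 26% | 50% | 81% |

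For example, at 70% with n = 10: 0.233 + 0.121 + 0.028 = 0.38. The second row shows the case where only 80% of the trained arm (10 × 0.8 = 8) is counted.

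**The session reading.** Ten participants give 10 × 24 = 240 sessions, but these are clustered within 10 people. The article gives no between-participant SD of attendance, so one is assumed. With SD 0.20, the 95% half-width of mean attendance is 2.262 × 0.20/√10 = 0.143, about 14 points. By the normal approximation, a true 70% then meets the cut 6% of the time and a true 90% meets it 94% of the time. Across SDs of 0.10 to 0.30, the chance at a true 70% runs from 0.1% to 15%. The unit therefore changes the answer materially.

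**Zero events.** The upper limit is 1 − α^(1/n).

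- n = 10, one-sided 95%: 1 − 0.05^(1/10) = 0.259.
- n = 10, two-sided 95%: 1 − 0.025^(1/10) = 0.308.
- n = 8: 0.312 and 0.369.

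A true event rate of 10% gives no events in 10 participants with probability 0.9^10 = 0.35. The trained arm is the main denominator, because the article defines an adverse event as one that stops exercise and is probably related to the exercise program.

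**The case against.** The strongest reply is that this is a declared pilot with 20 as a minimum, that wide intervals are ordinary at this size, and that interval methods usually belong in an analysis plan. The first two parts stand, and no power calculation is asked for. The third does not fully answer the point, because the article itself fixes the summary for these data and chooses an unsuitable one.

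Several stronger readings are tempting and are not supported:

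- **The compliance rule is close to a coin-flip.** On per-participant scoring it moves from 17% at a true 60% to 93% at a true 90%, so it does discriminate. A roughly even chance at the cut belongs to any rule based on a point estimate: at a true 80% it is still 57% with n = 80. On the session reading with modest spread, 10 people separate 70% from 90% fairly well.
- **Zero events will be declared safe.** No section says so. That is an inference a reader might draw from an unqualified count.
- **80% retention is a pass/fail cut.** It is a planning figure and is not among the Data analysis parameters.
- **Missing one parameter blocks the large trial.** The article says only that a statistician outside the study and the student researcher will assess the parameters at the end.
- **The Discussion overclaims precision.** The phrase "comprehensively assess the safety and feasibility" opens a list of domains and describes breadth, so it needs no change.

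**Conclusion.** The point holds in a limited form. The sample size is justified by feasibility and safety, but the stated summary hides how little about 10 trained participants can show, the 80% has no unit, and safety has no value to be read against. In size: 8/10 is compatible with true compliance from 44% to 97%, and no events in 10 excludes only rates above 26% (one-sided) or 31% (two-sided). The 17–38% chance that a true 60–70% meets the cut rests on two assumptions: per-participant scoring and exactly 10 trained. The intervals narrow if recruitment exceeds the minimum and widen if fewer than 10 are analysed. This is a defect of reporting and interpretation; it does not show that N = 20 is wrong for a pilot.

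**What to change.** In Data analysis:

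1. Replace mean and SD for these proportions and counts by n/N with exact binomial 95% intervals, for compliance, retention and participants with an event, showing the resistance training arm separately for compliance and events.
2. State whether the 80% refers to participants or sessions. If sessions, use an interval that allows for clustering within participants.
3. Read the 80% together with its interval, not as a stand-alone pass or fail.
4. Limit a favourable safety conclusion to 'no safety signal seen', with the upper bound printed beside it.

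Graded progression zones are not proposed. The documents give no basis for the cut-points, and Trial status shows that recruitment closed on 31 August 2019, so any zones would be set afterwards.

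The cost is wording and a few intervals, with no new data. The downside is that the pilot's conclusions become more modest.
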